## Abstract

**Introduction:**

Little is known about the effectiveness and safety of oxygen saturation (SpO2) thresholds in children admitted with respiratory distress. The current 90%–94% threshold could lead to prolonged administration of supplemental oxygen, increased duration of hospital admissions, distress for children and families, and healthcare costs. To balance reducing unnecessary oxygen administration and preventing hypoxia, a lower SpO2 threshold of 88% for oxygen supplementation in children has been suggested. This trial aims to test the hypothesis that a lower SpO2 threshold of 88% safely reduces the length of hospital stay in children admitted with respiratory distress when compared with a 92% SpO2 threshold and to assess its cost-effectiveness.

**Methods and analysis:**

This is a multicentre, open-label, randomised controlled trial with two parallel arms. A total of 560 children aged 6 weeks to 12 years admitted with a diagnosis of bronchiolitis, viral wheeze or lower respiratory tract infection will be recruited and equally randomised into an intervention or usual care arm. Intervention arm patients will receive supplemental oxygen if SpO2 falls below 88% or above 88% if deemed necessary by clinical staff. Control arm patients will receive supplemental oxygen if SpO2 falls below 92% or above 92% if deemed necessary by staff. The primary outcome is the time from admission to the time when all prespecified discharge criteria are met. Secondary outcomes are length of stay, safety (time to recovery, readmissions and paediatric intensive care admissions), quality of life, parental anxiety and societal costs. Patients are followed up by digital questionnaires up to 90 days postdischarge.

**Ethics and dissemination:**

This study has received approval from the research ethics committee (REC) of Leiden, Den Haag and Delft (EU CT number 2023-504817-56). Written informed consent will be obtained from parents or guardians. Parents of patients and patient representatives are involved in all stages of the study, from design to results, interpretation and dissemination. The results of this trial will be disseminated via lay publications, peer-reviewed scientific journals and academic conferences.

**Trial registration number:**

NCT06016244.

STRENGTHS AND LIMITATIONS OF THIS STUDYThis pragmatic trial and study procedures are very close to real-life practice, improving the generalisation of results and future implementation.The results of this study will enable the implementation of uniform oxygen saturation (SpO2) thresholds for nearly all children with respiratory distress due to a respiratory tract infection or viral wheezing, thanks to the broad age group and various diagnoses in the study population.Asthma patients aged 6 years and older are not included as there are safety concerns about lower SpO2 thresholds during the acute exacerbation phase.The open-label design introduces potential biases, which we will minimise by registering a fixed set of clinical parameters at oxygen start and stop to quantify potential biases, as well as a thorough training of physicians, nurses and trial staff.Safety evaluations in this study do not cover the long-term neurocognitive effects associated with either a lower or higher saturation threshold, as only short-term follow-up is described. However, follow-up studies are warranted to address the potential neurocognitive effects of lower or higher saturation thresholds in the long term.

## Introduction

 Acute respiratory distress is a common reason for hospital admission in children, caused by a variety of underlying diseases like bronchiolitis, viral wheeze, asthma or pneumonia.^1^ Primary treatment is the administration of supplemental oxygen.

Safe and effective oxygen therapy in children is crucial, as both undertreatment and overtreatment can have serious consequences. Supplemental oxygen is key in preventing tissue hypoxia during respiratory distress. However, overtreatment can lead to hyperoxia and oxidative stress, as shown in both mechanically ventilated children and adults.^2 3^ Moreover, aiming at higher oxygen saturations (SpO2) can prolong hospitalisation and cause unnecessary discomfort.

In clinical practice, supplemental oxygen is titrated on both respiratory distress and the recommended SpO2 threshold in current guidelines. However, the optimal SpO2 threshold that balances safety and effectiveness is not well established in children. Due to the lack of high-quality evidence, SpO2 thresholds for supplemental oxygen vary between (inter)national guidelines and hospitals and typically range from 90% to 94%.^4^,^6^

A 2014 Cochrane systematic review on supplemental oxygen therapy in children with lower respiratory tract infections revealed no studies on safe and effective SpO2 thresholds.^7^ In children up to 12 months with bronchiolitis, a randomised controlled trial has shown the safety of a 90% threshold compared with a 94% threshold.^8^ Children in the 90% saturation threshold group had an equivalent duration of cough and a faster return to normal health according to parents and were likely to be discharged 10 hours earlier than those in the 94% threshold group. Other studies on children with respiratory distress have shown similar effectiveness while maintaining safety with lower SpO2 thresholds ranging from 80% to 88%.^9^,^11^ These studies varied in quality and settings. A systematic review concluded that an 88% threshold deserves further study as a potentially effective and safe threshold.^12^ It is likely that the commonly applied SpO2 threshold of 92% is too high, resulting in children receiving too much oxygen, too often and for too long causing unnecessary and prolonged hospitalisations and increasing the burden of disease for these children and their parents.

Given the variation in guidelines and clinical practice, the lack of high-quality evidence and the significant potential benefits for patients and their parents, studies on effective and safe SpO2 thresholds for children with respiratory distress are urgently needed. This study aims to investigate whether an SpO2 threshold of 88%, compared with 92%, in children aged 6 weeks to 12 years admitted with respiratory distress, results in a safe reduction in length of hospital stay and is cost-effective from a societal perspective.

## Methods and analysis

### Trial design

This multicentre, open-label, randomised controlled trial with two parallel arms compares an 88% SpO2 threshold for starting and stopping supplemental oxygen (intervention group) with a 92% SpO2 threshold (control group). Data will be collected during admission and via digital questionnaires 7, 28 and 90 days after discharge (see table 1, participant timeline).

**Table 1 T1:** SPIRIT patient timeline

Time point	Enrolment	Allocation	Postallocation				
	−t_1_	0	Admission	Discharge	+7 days	+28 days	+90 days
Enrolment:							
Eligibility screen	X						
Informed consent	X						
Allocation		X					
Interventions:							
Intervention (88%)			X				
Control (92%)			X				
Assessments:							
Baseline			X	X			
Primary outcome: time to meeting all discharge criteria			X	X			
Length of stay, oxygen therapy, clinical characteristics			X	X			
PICU admission			X	X		X	
Readmissions or reassessments						X	
Recovery, duration of cough, duration of dyspnoea, time to return to school/daycare					X	X*	X*
Quality of life				X	X	X	X
Paediatric global health				X	X	X	X
Parental anxiety				X	X	X	
Cost-effectiveness			X		X		X

* Only if a patient has not recovered at +7 days time point.

PICUpaediatric intensive care unitSPIRITStandard Protocol Items: Recommendations for Interventional Trials

### Study setting

The trial will be conducted in the general paediatric wards of 10 general hospitals throughout the Netherlands. All sites are listed on the study website.^13^

The study commenced on 1 December 2022. The recruitment start date was 7 September 2023. The planned recruitment end date is 30 November 2025, and the trial end-date is planned for 1 December 2026.

### Participants

#### Inclusion criteria

To be eligible to participate in this study, a subject must meet all of the following criteria:

6 weeks to 12 years of age.Being hospitalised with respiratory distress due to bronchiolitis, viral wheeze or lower respiratory tract infection.Requiring supplemental oxygen as per usual care (SpO2<92% or on clinical indication as determined by the treating physician).

As a pragmatic approach, diagnoses are determined by the treating physician. They are free to use diagnostic tools and/or criteria as per usual care. The diagnosis of lower respiratory tract infection is any lower respiratory tract infection other than bronchiolitis. This can be a clinical diagnosis, not necessarily confirmed by chest radiograph or point-of-care ultrasound. In the case of overlapping diagnoses, the most prominent diagnosis is registered. If the diagnosis is changed during admittance, the diagnosis at enrolment will be used.

#### Exclusion criteria

A potential subject will be excluded from participation in this study if they meet any of the following criteria:

Children with pre-existing cardiopulmonary, neurological or haematological conditions (eg, congenital thoracic malformation, airway malacia, postinfectious bronchiolitis obliterans, childhood interstitial lung disease, primary immune deficiency or neuromuscular comorbidity).Children born <32 weeks gestational age.Children already included in other studies, which potentially interfere with this study.No stable internet access (needed for answering online questionnaires).No command of Dutch or English language.Children previously included in the current study.

As respiratory distress in children with an asthma attack is mainly driven by hypoxia, they are at risk of undertreatment in the acute phase of the attack.^14^ Therefore, children aged 6–12 years of age experiencing an asthma attack are excluded from this study.

### Interventions

#### Intervention group

Patients in the intervention group will receive supplemental oxygen if:

Their SpO2 levels drop below 88%, by:1%–2% for at least 15 min continuously.>2% for any amount of time.When indicated by the treating physician for clinical symptoms.

#### Control group

Patients in the control group will receive supplemental oxygen if:

Their SpO2 levels drop below 92%, by:1%–2% for at least 15 min continuously.>2% for any amount of time.When indicated by the treating physician for clinical symptoms.

Supplemental oxygen can be administered by either a face mask or nasal cannula, following local protocols. Patients are weaned of supplemental oxygen according to local protocols and based on the randomised SpO2 threshold.

Patients transferred to a paediatric intensive care unit (PICU) will receive standard care according to local PICU protocols, including SpO2 thresholds, and will be analysed according to protocol and included in the safety analyses.

To ensure adherence to the study protocol, both nurses and physicians at each centre will be trained to follow the study protocol. Any deviations from this protocol must be documented. Study protocol adherence is monitored by the registration of start and stop times of supplemental oxygen administration, including the reasons for starting and stopping, and clinical symptoms of the patient such as respiratory rate, heart rate and work of breathing. All other care is as usual. There are no prohibited concomitant care activities, drug prescriptions or interventions.

### Randomisation and allocation procedure

Patients are randomly assigned to either an 88% SpO2 threshold or a 92% SpO2 threshold. Allocation is done by the treating physician or nurse by drawing an opaque sealed envelope after obtaining written informed consent. The randomisation sequence is generated using a computer random number generator by a research team member not involved in recruitment or patient allocation. The sequence is based on a 1:1 block randomisation sequence, using varying block sizes, and is stratified for study site and age group (6 weeks to 1 year; 1 to 4 years and 4 to 12 years). Due to the nature of the intervention, participants, treating physicians and research team members cannot be blinded to the allocation. Although altering devices as done in the study of Cunningham *et al*^8^ would be ideal, device manufacturers are no longer willing to allow for such modifications due to tightened EU medical Devices Regulation requirements and liability concerns.

### Outcomes

#### Primary outcome

The primary outcome of this trial is the time from admission to when all prespecified discharge criteria are met. Prespecified discharge criteria are:

No need for supplemental oxygen for 4 hours, including a period of sleep for children aged <2 years.Clinically fit for discharge with normal or minimally increased respiratory rate AND no or mild respiratory distress, as judged by nurses and physicians using the Parshuram *et al*^15^ scoring system, commonly used in Dutch paediatric practice as part of the Paediatric Early Warning Scale.^16^No need for in-hospital feeding or medication by nasogastric tube.No need for in-hospital intravenous treatment.No need for in-hospital nebulised bronchodilator treatment.No need for in-hospital treatment with metered dose inhalator inhalations more often than every 3 hours.No need for high flow delivered by high flow nasal cannula or nasal prongs.

Nursing staff continuously monitor discharge criteria and register them when met. Clinical fitness for discharge is checked every 4 hours, starting 4 hours after oxygen therapy is first stopped. If oxygen therapy is not initiated, this criterion is checked every 4 hours starting 4 hours after randomisation. In clinical practice, the actual discharge time may be later than when all discharge criteria are met. The reasons for any delay in discharge will be documented.

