#### Patient screening and recruitment

Potential subjects and their parents/caregivers will first be informed using posters at the emergency department. Eligible subjects and their families will be screened by the attending physician and, if eligible, will be asked for informed consent by either their attending physician or an independent study nurse or doctor (see informed consent form, online supplemental file 2).

Conditional informed consent: For patients meeting all inclusion criteria at admission but not (yet) in need of supplemental oxygen, parents/guardians will be asked to sign informed consent conditionally. If the need for supplemental oxygen arises, consent is verbally confirmed and documented in the medical chart. If no supplemental oxygen is indicated during admission, the patient will not be included in follow-up and no additional data will be collected (see figure 1).

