**Figure 1 F1:**
[figure not shown]
Informed consent flow chart.

Study initiation: Study procedures begin when at least one parent/guardian provides written informed consent and the second has given verbal consent. Written consent from the second parent/guardian will be obtained within 72 hours after inclusion. The procedure is designed to accommodate emergency situations, where one parent is often present, ensuring the intervention can start as early as possible.

Informed consent process: Adequate time is provided for the informed consent process, allowing parents/guardians to receive information, ask questions, consult with family and consider their decision. For patients already on supplemental oxygen, study enrolment must be completed within 6 hours of the start of oxygen therapy to minimise time spent on supplemental oxygen outside the study protocol. For patients not yet on supplemental oxygen, informed consent is ideally obtained before the need arises but must be completed within 6 hours after the start of oxygen therapy. Beyond this timeframe, children are no longer eligible for participation.

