#### Statistical methods

##### Primary study parameter(s)

The time to meet all discharge criteria will be presented in hours. The primary analysis will be conducted on an intention-to-treat basis. Point estimates and uncertainty will be chosen based on the distribution of the data. The difference in hours between the groups will be analysed and tested for statistical significance, adjusting for centre and age and using a multilevel linear regression model for hospitals, with diagnosis and patient clinical parameters at presentation as covariates. A 12-hour difference is deemed clinically significant. Sensitivity analysis will include a per-protocol analysis of the primary outcome. For other time-to-event parameters, a Cox proportional hazards model will be used to estimate the intervention effect.

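### The primary outcome counts a variable wait before randomisation that the stated covariates do not remove; adjusting for it would gain a little precision at no cost

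*Protocol article*

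**What the plan says.** All references are to the protocol article.

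- **Clock.** Under Primary outcome, the endpoint is "the time from admission to when all prespecified discharge criteria are met".
- **Entry.** Under Inclusion criteria, a child must be "Requiring supplemental oxygen as per usual care". Under Patient screening and recruitment, parents may consent conditionally: "For patients meeting all inclusion criteria at admission but not (yet) in need of supplemental oxygen". Then, "If the need for supplemental oxygen arises, consent is verbally confirmed and documented in the medical chart". A child who never needs oxygen is not followed up.
- **Time limit.** In the informed consent text after Figure 1, "study enrolment must be completed within 6 hours of the start of oxygen therapy". No limit is stated that runs from admission.
- **Randomisation as its own time point.** Under Primary outcome, for children in whom oxygen is not initiated, the fitness check is made every 4 hours "starting 4 hours after randomisation".
- **Model.** Under Primary study parameter(s), the difference in hours is analysed "adjusting for centre and age and using a multilevel linear regression model for hospitals", "with diagnosis and patient clinical parameters at presentation as covariates". The interval from admission to randomisation is not named.
- **Planning figures.** Under Sample size and feasibility: difference 12 h, mean length of stay 72 h, SD 48 h, alpha 0.05, power 80%, 251 per arm, and 560 in total after 10% dropout.

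**The concern.** A child already on oxygen at arrival may be randomised within hours. A child who first needs oxygen on the second day is randomised then, but the clock has been running since admission. The outcome is thus the sum of a wait before allocation and a stay after it, and only the second part can respond to the threshold. The wait differs between children and so adds variance to the outcome. Covariates measured at presentation are recorded before the wait and can predict it only in part.

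What is at stake is precision in the primary comparison. The same origin is used for the secondary times counted from admission, including those analysed by Cox models, where the hours before randomisation are event-free by construction.

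**Working it through.** **1. The plan's own figure.** Two-sided alpha 0.05, power 0.80, difference 12 h, SD 48 h:

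n per arm = 2 × (1.960 + 0.842)² × (48/12)² ≈ 251.2 by the normal approximation, and 252.1 by the t-test.

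The stated 251 reproduces. With 10% dropout, 502/0.9 = 558 and 504/0.9 = 560, so 560 reproduces as well. t-test power at 251 per arm and SD 48 h is 79.8%, the baseline used below.

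**2. What the 48 h contains.** It is described as the SD that goes with a mean length of stay, so it belongs to a clock that starts at admission. Any wait before randomisation is already inside it.

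**3. Removing the wait, assuming independence.** Let s be the SD of the admission-to-randomisation interval. The documents do not give it, so s is an assumption shown over a range. If the wait is independent of later time, the SD after removing it is √(48² − s²).

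| s (h) | share of variance, s²/48² | remaining SD (h) | power, 251 per arm |
|---|---|---|---|
| 1.7 | 0.1% | 47.97 | 79.9% |
| 6 | 1.6% | 47.62 | 80.4% |
| 10.6 | 4.8% | 46.83 | 81.7% |
| 12 | 6.3% | 46.48 | 82.3% |
| 18 | 14.1% | 44.50 | 85.4% |
| 24 | 25.0% | 41.57 | 89.8% |

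**4. Which values of s are plausible.** A wait uniform over 0–6 h has s = 6/√12 = 1.7 h. Now mix late entrants with children uniform over 0–6 h. For a late share f entering uniformly over 0–L hours, the mean is fL/2 + 3(1 − f) and the mean square is fL²/3 + 12(1 − f).

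- f = 10%, L = 24: s = 3.8 h, power 80.1%
- f = 20%, L = 24: s = 5.0 h, power 80.3%
- f = 30%, L = 24: s = 5.8 h, power 80.4%
- f = 20%, L = 48: mean 7.2, mean square 163.2, s = √(163.2 − 7.2²) = 10.6 h, power 81.7%

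These scenarios gain about 0 to 2 percentage points.

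**5. Covariate or new clock, without independence.** Let ρ be the correlation between the wait and the later time, and hold the total SD at 48 h. The SD p of the later time solves s² + p² + 2ρsp = 48². A clock starting at randomisation has SD p. The admission clock with the wait as a linear covariate has residual SD p√(1 − ρ²).

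| s (h) | ρ | p (h) | power, new clock | residual SD (h) | power, covariate |
|---|---|---|---|---|---|
| 12 | −0.2 | 48.94 | 78.3% | 47.95 | 79.9% |
| 12 | −0.3 | 50.22 | 76.2% | 47.90 | 80.0% |
| 12 | 0 | 46.48 | 82.3% | 46.48 | 82.3% |
| 12 | +0.3 | 43.02 | 87.7% | 41.03 | 90.5% |

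In these cases the covariate version does not fall below the unadjusted 79.8%. The new clock can.

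**The case against.** The strongest reply is that nothing here is wrong. The trial asks about hospital stay, length of stay is an effect measure in the economic evaluation, and families experience the stay from admission. An admission clock measures that directly and is used consistently. The planning SD matches it. The exact covariate list may be completed in an analysis plan not shown here, and the phrase about clinical parameters at presentation is generic.

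Most of this stands, and it rules out four stronger readings that a reader might infer.

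- **Bias.** The wait ends before allocation, so it is balanced between arms in expectation and the difference in hours stays unbiased.
- **An underpowered trial.** The 48 h already includes the wait, so 251 per arm delivers what was planned. Adjustment would add to that; nothing is missing from it.
- **Distorted hazard ratios.** Event-free time before randomisation is also balanced in expectation. In an illustrative simulation (true log hazard ratio 0.262, 251 per arm, 20% entering over 0–48 h, 300 runs), outcomes lasting about 10 days gave a mean of 0.260 under the admission clock, delayed entry and the randomisation clock alike. For outcomes of about 60 h, delayed entry gave 0.257 and the admission clock 0.255.
- **The clock should start at randomisation.** Step 5 shows that this can lose power.

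The analysis-plan argument does not fully dispose of the point. The article states both the clock and the covariates, and the interval is not among those covariates.

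**Conclusion.** The point holds as an optional gain in precision. The primary outcome includes a variable interval before allocation, and the stated covariates leave it in the residual. The documents do not support any claim of bias or of a shortfall against 80% power.

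The likely gain is about 0 to 2 percentage points of power. Gains of 5 points or more need an interval SD near 18 h, hence many children entering a day or more after admission, and nothing in the article suggests that.

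The size rests on three assumptions: a spread for the interval that the documents do not give; independence of wait and later stay in steps 3 and 4; and an unadjusted t-test as the baseline. The other planned covariates will reduce the residual SD and may already explain part of the wait.

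That randomisation waits for the need for oxygen is inferred from the inclusion criterion and the conditional-consent text. The article speaks of children who meet all inclusion criteria without yet needing oxygen, although that need is itself an inclusion criterion. The wording should be reconciled so that the moment of randomisation is explicit.

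**What to change.** - Keep the admission-based endpoint. Pre-specify the admission-to-randomisation interval, in hours, as a baseline covariate in the primary multilevel linear model.
- Do not replace the endpoint with hours from randomisation. That may be reported as a sensitivity analysis without the interval as a covariate, because once the interval is a linear covariate the two clocks give the same treatment estimate.
- Optionally, use delayed entry at randomisation in the Cox models for times counted from admission. This is a technical refinement with negligible expected effect.
- State when randomisation takes place for children with conditional consent.

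The cost is a few lines of analysis wording, fixed before outcome data are examined by arm, since a covariate added later in an open-label trial would look chosen from the data. No extra patients or visits are needed. The endpoint already uses the admission time, and the 4-hourly checks already refer to the randomisation time.
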